### Injury assessment

Participants will be asked to complete their allocated treatment two days per week before their running sessions for maintenance following the initial 8 weeks of training. The primary outcome measure for this portion of the research project will be running-related injuries. During the 6-month follow up period, running injuries will be tracked and documented for each participant using StudyTRAX, a web-based Electronic Data Capture system. Injuries will be identified using the “any physical complaint” definition as “any physical complaint developed in relation to running activities and causing restriction in running distance, speed, duration, or frequency”[70, 71]. Injuries reports will be completed weekly using the questionnaire that has previously been validated for overuse injuries[72]. An additional question will be added to this questionnaire asking the participant if they experienced any “physical complaint that prevented them from being fully able to participate in running activities”[72, 73]. If a participant answers “yes” to the final question, they will be contacted directly and asked to fill out the “time-loss” injury questionnaire using a “time-loss injury” questionnaire that was adapted for running injuries[74]. All “time-loss” injuries occurring during this time will be assessed by a physiotherapist. Injury incidence and severity for overuse injuries will be quantified by the average weekly incidence and severity scores from the overuse injury questionnaire[72]. Subjects will be asked to complete a physical activity log documenting their running routines as the number of minutes of running exposure on a weekly basis[42]. This will provide information regarding the running frequency per week as well as the length of time of each run in minutes. Due to funding limitations, heart rate monitors and GPS tracking were not available. Therefore, no information will be available regarding the type of run (tempo, steady state, intervals). Injury incidence and severity for acute injuries will be quantified by injury rate (number of injuries/1000 running hours) and the number of days taken away from running due to the injury[72]. Participants will also self-report their protocol adherence every week during the eight week intervention[75].

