#### Hypotheses

All hypotheses are made based on comparisons between each of the training groups and the control group.Isolated ankle strengthening will increase ankle isokinetic strength but not strength at the knee or hip joints.Isolated ankle strengthening will significantly decrease joint movements and joint moments in the frontal and transverse planes at the ankle during over ground and treadmill running.Functional balance training will significantly increase ankle and knee and hip isokinetic strength.Functional balance training will significantly decrease joint movements and joint moments in the frontal and sagittal planes at the ankle, knee and hip joints during over ground and treadmill running.Functional balance training will significantly reduce the center of pressure movement magnitude, increase the regularity of the center of pressure time series and improve performance on the Star Excursion Balance Test.Injury rates will be lower for the functional balance training group and the isolated ankle strengthening group compared to the activity matched control group.

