**Twenty-five minute training routine for the isolated ankle strengthening group.**

**Table 2 Tab2:** **Twenty-five minute training routine for the functional balance training group**

Category		Movement				Duration	
Aerobic		Side-to-side shuttle, high knee skipping, light running				1 min	
Static stretch		groin, hamstrings, quadriceps, calves (30 seconds each)				2 min	
Dynamic stretch		Buttock Kicks – 1 minutes				2 min	
		Leg Swings – Side, 30 seconds					
		Leg Swings – Front, 30 seconds					
		Total time				5 min	
Balance weeks 1,2		Balance weeks 3,4		Balance weeks 5,6		Balance weeks 7,8	
Movement	Reps	Movement	Reps	Movement	Reps	Movement	Reps
Lunges: forward and backward	10 per side	Lunges: round the clock	5 per side	Lunge forward onto BOSU ball and backwards off of BOSU ball	10 per side per condition	Lunge forward onto BOSU ball and backwards off of BOSU ball	20 per side per direction
Squat: bipedal, box touch	10	Squat: bipedal on BOSU, ball facing down	10	Squat: single leg	10 per side	Squat: single leg mini squat on BOSU ball, ball facing up	10 per side
Hop in a box formation: bipedal	5 per direction	Hop in a box formation: single leg	3 per side per direction [6 per side in total]	Hop onto BOSU: Bipedal, ball facing upwards	10	Hop onto BOSU: single leg, ball facing upwards, forward, and side	5 per side per direction
Single leg stance: eyes open, eyes closed, variations with lower limb movements for increasing difficulty	5 per visual condition, 30 sec	Single leg stance: eyes open, eyes closed, variations with lower limb and trunk movements for increasing difficulty	5 per visual condition, 30 sec	Single leg stance on BOSU: ball facing upwards	5 per visual condition, 30 sec	Single leg stance on BOSU: ball facing upwards, variations in arm and torso movements.	5 per visual condition, 30 sec
Lateral Jump: left to right side	20 per side	Star Jump: left to right side	5 per side	Star jump: right leg to right leg, left leg to left leg	3 per side	Star jump: right leg to right leg, left leg to left leg, increasing jumping distance	3 per side

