Acute and overuse injury rates will be quantified separately due to the difference in injury definition[78]. Injury rates (number of injuries/1000 running hours) and 95% confidence intervals will be estimated. In an attempt to avoid the effects of dropout and adherence, an intent-to-treat analysis will be used. A multivariate Poisson regression analysis will be used to estimate incidence rate ratio (IRR) between the functional balance training group and the control group as well as between the isolated ankle strengthening group and the control group while controlling for age, gender and any other differences in baseline characteristics. Descriptive statistics for the amount of time missed from running due to injury (mean and standard deviation) will be calculated for both groups[79].

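### The injury definition (arising from running) and the added time-loss question (any cause) are not reconciled, so injuries caused by the assigned routines fall outside the outcome on which arms are compared

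*Protocol article*

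**What the plan says.** All references are to the protocol article.

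- **Outcome.** Injury assessment: "The primary outcome measure for this portion of the research project will be running-related injuries".
- **Definition.** The same section counts "any physical complaint developed in relation to running activities and causing restriction in running distance, speed, duration, or frequency". Both parts must hold: the complaint arises from running, and it restricts running.
- **Second route.** A further weekly question asks about any "physical complaint that prevented them from being fully able to participate in running activities". This wording sets no condition on cause. A yes leads to direct contact and a time-loss questionnaire adapted for running injuries. Time-loss "injuries occurring during this time will be assessed by a physiotherapist".
- **Analysis.** "Acute and overuse injury rates will be quantified separately due to the difference in injury definition". "Injury rates (number of injuries/1000 running hours) and 95% confidence intervals will be estimated". A Poisson model then compares each training arm with control.
- **Routines.** Treatment arms asks all three groups for five sessions a week. The two training arms do 20 minutes of specific work after a 5-minute warm-up; control does a 25-minute warm-up. The balance routine in weeks 7 and 8 (Table 2) includes "Hop onto BOSU: single leg, ball facing upwards, forward, and side". Two sessions a week continue as maintenance after week 8.
- **Hypothesis.** "Injury rates will be lower for the functional balance training group", and likewise for the strength group, each against control.

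**The concern.** The trial asks whether the two programmes prevent injury, and each programme is itself physical work done at home. A sprain or overload from the routine can stop someone running just as a running injury can. Under the stated definition it is not an event. Under the added question it is reported and assessed. The article does not say which wording decides whether it enters the rate.

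Both readings cause difficulty. If such complaints are set aside, a programme could move injuries from running into training and still show a lower running-injury rate. If they are counted, the definition is contradicted, and running hours are the wrong exposure for them.

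Attribution will also be hard. On running days the routine comes immediately before the run (Treatment arms), complaints are self-reported, and the Randomization procedure section describes the design as non-blinded. If cause is not recorded when a complaint is reported, a later analysis plan cannot reliably recover it.

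**Working it through.** **The plan's own figures.** The article gives no expected injury count or power for injuries. The 40 per arm comes from the ellipse-area calculation: 2 × (1.96 + 0.84)² / 0.71² is about 31.1, which rounds up to 32, and 32 / (1 − 0.20) = 40. Both figures reproduce.

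**Step 1: exercise exposure specific to a training arm, at full adherence.**
- First 8 weeks: 5 × 8 = 40 sessions × 20 min = 13.3 h per participant.
- Maintenance, assuming sessions of the same length: 2 a week for 18 weeks is 36 × 20 min = 12.0 h. For 26 weeks it is 52 × 20 min = 17.3 h. The range reflects whether the 6 months include the first 8 weeks.
- Per arm of 40: 40 × 25.33 = 1013 h to 40 × 30.67 = 1227 h.

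**Step 2: expected control running injuries.** Inputs are the 26-85% yearly incidence (Background), 40 per arm and 6 months. A constant hazard and no dropout are assumed.
- C = 40 × (−ln(1 − p)) / 2
- p = 0.26: 40 × 0.301 / 2 = 6.0
- p = 0.85: 40 × 1.897 / 2 = 37.9

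**Step 3: excess of exercise injuries that offsets a running benefit.** Let r be the running-injury rate ratio, and let T and K be exercise-caused injuries in the training and control arm. With equal running hours:
- Total-injury ratio = (C × r + T) / (C + K)
- This equals 1 when T − K = C × (1 − r)
- With an assumed r = 0.5: 6.0 × 0.5 = 3.0 at the low end and 37.9 × 0.5 = 19.0 at the high end.
- At the low end, 3.0 injuries over 1013 to 1227 h is about 2.4 to 3.0 per 1000 h of specific exercise.
- At the high end, three extra injuries would only move the ratio from 0.50 to (18.97 + 3) / 37.94 = 0.58.

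**Step 4: a weaker running effect.** Here r = 0.8, and C, T and K are all assumed.

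| C | T | K | Total-injury ratio |
|---|---|---|---|
| 20 | 2 | 0 | 18/20 = 0.90 |
| 20 | 4 | 0 | 20/20 = 1.00 |
| 10 | 2 | 0 | 10/10 = 1.00 |
| 10 | 4 | 0 | 12/10 = 1.20 |
| 20 | 2 | 2 | 18/22 = 0.82 |
| 20 | 4 | 4 | 20/24 = 0.83 |
| 10 | 2 | 2 | 10/12 = 0.83 |
| 10 | 4 | 4 | 12/14 = 0.86 |

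With equal exercise injuries in both arms the ratio moves only from 0.80 to between 0.82 and 0.86. With r = 1.0 and T = K it stays at 1.00. The size of the problem therefore depends on the excess T − K, which the article gives no means to estimate.

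**The case against.** A reader might infer that exercise injuries go wholly unseen and that the comparison is tilted towards both training arms. The article does not support that.

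- **Capture.** The time-loss question has no condition on cause and leads to a physiotherapist. A sprain that stops running would probably surface, and acute and overuse injuries have different definitions. What is unsettled is how such a case is classified and whether it is reported by arm.
- **Same rule in every arm.** Control also has an active routine, including 5 minutes of shuttles, skipping and light running against 1 minute in the balance arm (Tables 1 and 2). Injuries from it fall outside the definition too. A tilt needs more exercise injuries in training than in control. That is plausible for single-leg hops onto an unstable device. It is uncertain for the elastic-band arm.
- **Running hours.** Someone hurt in training who runs less also adds less to the denominator. Lost hours do not by themselves lower the rate; the event is simply absent from it.
- **Choice of outcome.** Running-related injury is a legitimate outcome, and the Sample size section calls the injury part a pilot. A condensed article may also leave harms recording to the full protocol, so its absence here is no fault. The time-loss questionnaire may already record the causing activity; this cannot be seen.

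All of this stands, and it narrows the point. It does not remove the unreconciled wordings, or the fact that the stated comparison is per running hour only. Pilot status does not lessen the value of a clear rule, since the Sample size section wants these incidence figures for planning later trials.

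**Conclusion.** The point holds in a limited form. The defined injury outcome requires running as the cause, the added question does not, and the article does not say which governs a complaint caused by the assigned routine. On the stated definition such injuries lie outside the outcome compared between arms. The running-injury rate ratio can therefore not be read as net injury prevention.

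Direction and size are conditional. The ratio overstates net prevention only if exercise injuries are more frequent in a training arm than in control. Under a constant hazard, 40 per arm, equal running hours and an assumed ratio of 0.5, the offsetting excess is 3 to 19 injuries. It would be wrong to infer that three such injuries would cancel the benefit in general: that is true only at the low end of the 6-to-38 range. The ratio and the exercise-injury counts are assumptions, not figures from the article. This is an inexpensive improvement worth making, not a demonstrated bias.

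**What to change.** 1. Keep running-related injury as the primary outcome of the injury part.
2. Add one item to the weekly questionnaire recording whether each complaint arose during running or during the assigned warm-up or training routine.
3. State in Injury assessment that time-loss complaints caused by the routine are not counted as running-related but are tabulated.
4. Beside the rate per 1000 running hours, report exercise-caused and total running-limiting injuries by arm, as counts and per participant-time.
5. Base any conclusion about injury prevention on both sets of figures.

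The cost is one weekly item and one table. Sample size, randomisation and the routines do not change. The downsides are slightly more participant burden and a net result that may look less favourable. Attribution will remain uncertain when the routine is done just before a run; the total count by arm is useful there because it does not depend on attribution.

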#### Analysis

Descriptive statistics of baseline characteristics of the participants in each group will be reported (mean, standard deviation, 95% confidence intervals). These will be presented in tabular form in order to determine if the groups were well balanced with respect to age, mass, height, weekly mileage and running experience[76].

For the isokinetic strength measurements, the peak torque of the three maximal isokinetic contractions will be identified. For postural control, the average entropic half-life in the medio-lateral and anterior-posterior direction will be calculated for the eyes open and eyes closed single limb tasks in the ML and AP direction. Additionally, the average COP 95% ellipse area, average COP path length, and average SEBT reach distance will be calculated. For the over ground running trials, a discrete analysis will be completed using Kintrak software (Human Performance Laboratory, Calgary, Canada) to calculate three-dimensional joint angular displacements, and moments for the ankle, knee and hip joints. Specifically, peak ankle eversion/inversion angle and moment, peak knee ab/adduction angle and moment, peak knee internal/external rotation angle and moment, peak hip ab/adduction angle and moment and peak hip internal/external rotation angle and moment during the stance phase will be calculated. All variables will be normalized to the stance phase of the right foot where heel contact and toe off will be identified as crossing a 15 N threshold. Additionally, a vector-based analysis approach (iterative support vector machine [SVM]) will be used to determine the classification rate of subjects following training as well as to identify the movements that have changed following training using the entire data set rather than discrete time points for the treadmill run[77]. A multivariate linear regression will be used to determine whether the change from baseline to the end of training in each variable for each training group is significantly different from the change found in the control group while controlling for age, gender, and any other baseline differences between the groups.

Acute and overuse injury rates will be quantified separately due to the difference in injury definition[78]. Injury rates (number of injuries/1000 running hours) and 95% confidence intervals will be estimated. In an attempt to avoid the effects of dropout and adherence, an intent-to-treat analysis will be used. A multivariate Poisson regression analysis will be used to estimate incidence rate ratio (IRR) between the functional balance training group and the control group as well as between the isolated ankle strengthening group and the control group while controlling for age, gender and any other differences in baseline characteristics. Descriptive statistics for the amount of time missed from running due to injury (mean and standard deviation) will be calculated for both groups[79].

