### Sample size

Exploratory power analyses were completed for multiple biomechanical variables that will be tested in this study. Sample size was determined based on a sample size calculation using previously published data on the effects of balance training on the 95% ellipse area of the center of pressure as this was the largest reasonable sample size needed for the variables in this study[37]. It was found that in order to achieve 80% statistical power with an α = 0.05, 32 subjects would be needed to detect a change between training group and the control group with respect to the change in the 95% ellipse area following training with an effect size of 0.71. Assuming a 20% drop out rate, 40 subjects will be recruited for each of the groups in this project. Due to the sample size, the injury portion of this study will be a pilot RCT for developing a running injury prevention program. The information found in this study regarding the incidence of injury in each group will be critical for developing future RCTs investigating the impact of these interventions on running injury prevention.

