### Randomization procedure

In order to protect against selection bias, subjects will be randomly assigned to one of the three groups. The generation of an unpredictable randomized allocation sequence will be completed using randomization.com through the use of a random allocation scheme (one block, size 120) with a 1:1:1 allocation ratio between the three groups. This randomization procedure was chosen to avoid selection bias with predictable random assignments using smaller block sizes in a non-blinded study design. This task will be completed by an individual that is not involved in the trial. In order to ensure allocation concealment, sequentially numbered, opaque, sealed envelopes (SNOSE) will be used. Once potential subjects have provided written, informed consent, they will sequentially draw an envelope and write their details on that envelope before opening to determine their group allocation. All envelopes will be similar in appearance and weight and cardboard will be placed within the envelope in order to make it impermeable to light.

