#### Measurements

Baseline characteristics will be collected for each subject including height, mass, running frequency, running experience, and injury history. Subjects will attend one testing session prior to the training intervention and one testing session immediately following the training intervention (within 9 weeks from baseline) for biomechanical data collection. These testing sessions will involve the collection of isokinetic strength data and the collection of lower extremity running mechanics (kinematics and kinetics) and postural control (dependent variables). Postural control will be assessed as balance deficits have previously been shown to be predictive of future ankle sprains in healthy athletes[57–59].

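### Beyond age and gender, covariates are chosen by observed baseline imbalance, and the outcome's own baseline value is not a fixed covariate in the change-score models

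*Protocol article*

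**What the plan says.** All references are to the protocol article.

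- **Biomechanical outcomes (Analysis).** Each variable's pre-to-post change is compared between each training arm and the controls by linear regression. The adjustment clause reads: "while controlling for age, gender, and any other baseline differences between the groups".
- **Injuries (Analysis).** The Poisson model compares each training group with control "while controlling for age, gender and any other differences in baseline characteristics".
- **How balance is judged (Analysis).** A descriptive table is used to decide whether the groups are balanced on age, mass, height, weekly mileage and running experience. No test or threshold is given.
- **What is available (Measurements).** "Baseline characteristics will be collected for each subject including height, mass, running frequency, running experience, and injury history". Strength, running mechanics and postural control are all tested once before training and once after it, so each biomechanical outcome has a baseline value.
- **Allocation (Randomization procedure).** The scheme is "one block, size 120) with a 1:1:1 allocation ratio between the three groups", with no stratification; the section describes the design as non-blinded.
- **Sample size.** The requirement is stated as "in order to achieve 80% statistical power with an α = 0.05, 32 subjects would be needed". The target contrast, training arm against controls, is specified "with respect to the change in the 95% ellipse area following training with an effect size of 0.71". Allowing for 20% dropout, the plan recruits 40 per group.

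**The concern.** In a randomised trial, baseline differences between groups arise by chance. A covariate earns its place by how well it predicts the outcome, not by whether it looks unbalanced. For a repeated measurement the natural candidate is the same measurement before training, and neither regression sentence names it.

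Three things are at stake.

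1. **Precision.** A change score implicitly fixes the slope on baseline at one. When the pre/post correlation is below one, that subtracts too much, and the contrast is noisier than one that estimates the slope.
2. **Conditional bias.** If one arm starts higher by chance, regression to the mean carries part of that difference into the change-score contrast. Adjusting for baseline removes it.
3. **Discretion.** No criterion defines a difference, and it is unclear whether the clause covers baseline outcome values or only participant characteristics. Two analysts following the text could fit different models, and in a non-blinded trial nothing stated keeps that choice separate from the results.

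**Working it through.** **Step 1. Reproduce the sample size.** Inputs from Sample size: effect size 0.71 on the change, α = 0.05 (taken as two-sided, since one-sided gives 25), power 80%, dropout 20%.

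n per group = 2(1.960 + 0.842)² / 0.71² = 2 × 7.849 / 0.5041 = 31.1, so 32. Then 32 / (1 − 0.20) = 40. Both stated figures reproduce. Power at 32 per group is 81% (normal approximation) or 80% (t-based). This is the power of an unadjusted change score.

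**Step 2. Variance with and without the baseline covariate.** Let r be the correlation between the pre- and post-training values, with equal variances at the two visits. In units of the outcome variance:

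- change score: 2(1 − r)
- ANCOVA (adjusted for baseline): 1 − r²
- ratio: (1 − r²) / [2(1 − r)] = (1 + r)/2

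The document gives no r, so a range is assumed. Because age and gender are in the model either way, r is best read as the correlation remaining after them.

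| Assumed r | Variance ratio | Equivalent extra subjects, 1/ratio − 1 | n per group for 80% power | Power at 32, formula |
|---|---|---|---|---|
| 0.3 | 0.65 | 54% | 21 | 94% |
| 0.5 | 0.75 | 33% | 24 | 91% |
| 0.7 | 0.85 | 18% | 27 | 87% |
| 0.8 | 0.90 | 11% | 29 | 85% |
| 0.9 | 0.95 | 5% | 30 | 83% |

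**Step 3. Does adjusting only when baseline looks imbalanced recover the gain?** Simulation with three arms of 32, a true effect of 0.71 SD of change, and 4,000 runs per setting. The conditional rule adjusts for baseline only when a three-group test of baseline gives p < 0.05; that trigger is assumed, since the protocol states none.

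| r | Change score | Adjust only if imbalanced | Always adjust |
|---|---|---|---|
| 0.3 | 81% | 82% | 93% |
| 0.5 | 79% | 79% | 89% |
| 0.7 | 80% | 80% | 85% |
| 0.9 | 80% | 80% | 82% |

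The trigger fired in about 5% of trials, so almost none of the gain is recovered. Under no effect, the conditional rule rejected in 4.1% to 4.7% of trials, so a fixed version of the rule does not inflate type I error.

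**Step 4. Conditional bias.** At 32 per arm the standard error of a baseline difference is √(2/32) = 0.25 SD. A baseline difference of that size shifts the change-score contrast by (1 − r) × 0.25: 0.125 SD at r = 0.5 and 0.05 SD at r = 0.8 (SD of the outcome).

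**Step 5. How often would chance alter the covariate list?** Age is always in the model, so four listed characteristics remain: mass, height, weekly mileage and running experience. Assume independence and a p < 0.05 trigger. With one three-group test each, 1 − 0.95⁴ = 19%. With two contrasts each sharing the control arm (correlation 0.5), the chance per characteristic is 9.1%, and 1 − (1 − 0.091)⁴ = 32%. Correlated characteristics, such as height and mass, would lower both figures.

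**The case against.** The strongest reply is that nothing here is invalid. Randomisation makes the change-score contrast unbiased over repeated trials, the objectives and the sample size are both framed on change, and the planned power is met. Age and gender are fixed in both models, so the data-dependence is partial. The gain from baseline adjustment rests on a correlation the document does not give, and near 0.9 it is small. The injury part is declared a pilot. The cut-off for calling something a difference is a detail that an article may leave to an analysis plan that is not shown.

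Most of this stands and sets the limits of the point. It does not remove it: the article does more than stay silent on covariates, because it states a selection rule, and the rule selects on the wrong property.

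Several stronger readings are tempting, and the document does not support them:

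- **That injury history is left out of the injury model.** It is absent from the balance list, but Measurements counts it among the baseline characteristics, and the injury clause covers any that differ. It is a candidate without a fixed place. The document gives no prognostic strength for it, so its benefit cannot be sized.
- **That the injury model would be overloaded because control-arm injuries are few.** The Poisson model uses events from all groups, so control-arm events alone are the wrong count.
- **That the model will necessarily differ from outcome to outcome.** If the clause means participant characteristics only, one set would serve all outcomes. It would vary mainly if baseline outcome values are also screened, and the text does not settle this.

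**Conclusion.** The point holds as one of efficiency and prespecification. Two regressions fix age and gender and leave the remaining covariates to chance imbalance without a criterion, while the most obvious prognostic covariate for each biomechanical variable is measured but not fixed.

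The size depends on an assumed r and on equal variances at the two visits. For r of 0.5 to 0.8, ANCOVA variance is 75–90% of change-score variance. At 32 per group, power for the planned effect rises from about 80% to 89–91% at r = 0.5 and 85–87% at r = 0.7 (simulation and formula), but only to 82–83% at r = 0.9. Under the assumed trigger, adjusting only on imbalance captures almost none of this.

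A reader might infer that the trial is underpowered by its own standard or that its type I error is inflated. Neither follows: the stated numbers reproduce, and a fixed version of the rule keeps type I error below 5% in simulation. That result covers a rule fixed in advance; it does not cover free choice by an analyst who has seen the results.

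**What to change.** In the Analysis section:

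1. **Biomechanical outcomes.** Replace the open-ended clause with a closed list for each variable: group, that variable's own pre-training value, age and gender. With baseline in the model, analysing the change or the post-training value gives the same group contrast, so the objectives can stay worded as change.
2. **Injury model.** Replace the matching clause with a short covariate list fixed before the data are seen. It may include injury history, which is already collected, though the document gives no basis for sizing the benefit.
3. **Baseline table.** Keep it, but as description only, with no role in choosing covariates.

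The cost is a change of wording. Every covariate named is already to be collected or measured, and the 32 evaluable and 40 recruited per group can stand.
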